### Methods of randomization and bias minimization

Once the informed consent has been obtained, the patient will be assigned 1:1 by the investigator to either the control or intervention group according to the allocation sequence generated by the randomization program. Only the researchers who signed the informed consent had access to this list which was concealed from the principal investigator.

The data for the screening will be obtained from the clinical records program of the Hospital Clínic de Barcelona, where the data of patients who required admission to the ICU, as well as days of admission, will be reviewed by the members of the research team in order to verify whether they are eligible or not.

Screening for patients will be done monthly. Enrolment is expected to be completed within 3 to 6 months. The baseline visit will take place between 4 to 6 weeks after hospital discharge. Follow-up visits will take place at 3 and 6 months after discharge (Fig. 2.)

Patients will be encouraged to remain in the study during each interview by giving them feedback about the importance of their collaboration. Participants who decide to drop out during follow-up will be asked about the reason for it, and all their answers will be recorded.

The database will be paper-based and electronic data entry will also be used using FileMaker. Only three research team members will obtain access to this program. case report forms (CRF) will be kept in the hospital files and all data will be available on the web after study finalization.

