### Study population

Adult patients will be enrolled if they fulfil at least one of the following Inclusion criteria: (1) had SARS-CoV-2 infection, confirmed with a respiratory tract sample using PCR-based tests, (2) had an Acute Physiology And Chronic Health Evaluation (APACHE II) score over 14, (3) ICU stay over 10 days, (4) acquired weakness in ICU [14] (Supplement, Definition D1), (5) delirium during ICU [14] (Supplement Definition, D2), and 6) acceptance to participate in the study by signing the informed consent form.

The exclusion criteria are as follows: (1) patients with non-confirmed SARS-CoV-2 infection according to WHO guidance [15], (2) central ervous system degenerative diseases or terminal illness (Supplement, Definition D3), (3) terminal illness (Supplement, Definition D4) [16], (4) insufficient understanding of the Spanish language, (5) patients with whom it would be difficult to complete follow-up, and (6) not willing to sign the informed consent form.

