### Blinding

This is a single-blind study. Visits will be carried out by an investigator with adequate training in questionnaire administration. This investigator will not participate in the intervention or the evaluation of the results. The intervention will be performed by two researchers (a pain physician and a psychologist). These researchers will not participate in the questionnaire and baseline data collection nor in the data analysis. Researchers who analyze the results will not participate in the questionnaire and baseline data collection or program intervention.

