### Recruitment and participant timeline

Patients who are eligible for the study will be contacted approximately 1 month after discharge from the hospital, they will be informed about the study, and they will be asked to participate. Those who accept to participate will have to complete a baseline visit the following week. Informed consent will be obtained by one of the investigators (Supplement, Figure F2).

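### The allocation list is open to the researchers who sign consent and hidden only from the principal investigator, with no stated safeguard against foreknowledge, so selection bias is possible

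*Protocol article*

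**What the plan says.** All references are to the protocol article.

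- **Who assigns, and when**: "Once the informed consent has been obtained, the patient will be assigned 1:1 by the investigator to either the control or intervention group", and this is done "according to the allocation sequence generated by the randomization program" (section Methods of randomization and bias minimization).
- **Who holds the sequence** (same section, next sentence): "Only the researchers who signed the informed consent had access to this list which was concealed from the principal investigator".
- **Who takes consent** (Recruitment and participant timeline): "Informed consent will be obtained by one of the investigators".
- **Who checks eligibility** (Methods of randomization and bias minimization): hospital records "will be reviewed by the members of the research team in order to verify whether they are eligible or not". Screening is monthly.
- **A criterion that needs judgement** (Study population, exclusion criteria): "patients with whom it would be difficult to complete follow-up".
- **Who runs visits** (Blinding): "Visits will be carried out by an investigator with adequate training in questionnaire administration". The same section keeps questionnaire collection, intervention and analysis in separate hands.
- **Order of events** (Baseline visit): information, then consent, then randomization.

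**The concern.** Allocation concealment protects the moment of entry. It works only if the people who decide whether, when and how a patient enters cannot know the next assignment. The article states who could see the list, and the group it names is the group that signs consent. The one person from whom the list is said to be hidden is not described as enrolling anyone.

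If a recruiter knows the next assignment, the choice of whom to contact first, how the study is presented, or who counts as hard to follow can come to depend on the arm. The two arms may then differ in prognosis from the start. That would bias the primary comparison of quality of life at 6 months, and an intention-to-treat analysis would carry the bias forward. Adjustment can deal with measured differences only.

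**Working it through.** No figure in the article depends on this point, so there is none to reproduce. The check is a reading of the sections together, followed by an illustration.

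**Reading**

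1. The list is the allocation sequence, because the sentence on access directly follows the one that introduces the generated sequence.
2. Its holders are the researchers who signed consent. Recruitment and participant timeline says an investigator obtains consent, so the natural reading is the researchers who obtain and countersign it.
3. The article describes no central or web allocation, sealed envelopes, independent list holder or release of one assignment at a time.
4. Randomizing after consent fixes when the assignment is made. It does not limit what a list holder knows beforehand.
5. There are routes by which such knowledge could act. Screening is monthly and eligible patients are then contacted, so several candidates may be waiting and the order of contact can vary. The follow-up exclusion is a judgement. The Discussion expects severely affected patients to have trouble attending visits, and the intervention arm has medical visits while control follow-up is by telephone. Expected difficulty of follow-up may therefore relate both to prognosis and to arm. This route exists only if the list holders apply the criterion, which the article does not say.
6. Separating questionnaire, intervention and analysis roles under Blinding protects later steps. It does not protect the sequence before assignment.

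**Illustration (SD and bias are assumptions)**

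- SD: not stated. Under Sample size, a control mean of 50 and a 20% difference give 10 points, with one tail at 0.05, 80% power and 42 per arm. The normal approximation gives 10 × √(42/2) / (1.645 + 0.842) ≈ 18.4. The t-test version gives about 18.3, which is used here.
- Patients per arm: 102 × 0.8 / 2 = 40.8, taken as 41. The plan's own target of 42 changes little.
- True effect: 0. Assumed prognostic imbalance b: 3, 4 or 5 points.
- Standard error: 18.3 × √(2/41) = 4.04.
- Non-centrality: δ = b / 4.04. The rejection rate is P(|T| > t(0.975; 80 df)), with T non-central t with 80 degrees of freedom and non-centrality δ.

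| b (points) | δ | Rejection rate under no effect |
|---|---|---|
| 0 | 0 | 5.0% |
| 3 | 0.74 | 11.4% |
| 4 | 0.99 | 16.5% |
| 5 | 1.24 | 23.1% |

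Because the SD is itself assumed, the same formula with SD from 15 to 25 gives about 15% down to 8% for b = 3, and about 32% down to 15% for b = 5. These rates would follow from any imbalance of that size, whatever its cause. They show how sensitive a trial of this size is and say nothing about what this list produced.

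**The case against.** The best case for the plan is that the sentence says who had access and not when. It could mean that a researcher learned each assignment once that patient's consent was signed, which would fit the stated order of consent and then randomization. A journal article may leave the release mechanism to the full protocol.

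Part of this stands. A reader might infer that assignments were in fact known ahead and that allocation was unconcealed in practice. The documents do not show that. But the sentence is a positive statement about access, so the problem is more than an omitted detail. If release was one at a time, the sentence misdescribes the procedure and needs correcting.

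Two further inferences are tempting and unsupported:

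- **That the list holders also judge eligibility.** Eligibility review is given to members of the research team and consent to one of the investigators. Nothing says they are the same people, and the follow-up exclusion might be applied at records screening, before contact.
- **That the outcome assessor holds the list.** Consent is taken at the baseline visit, and visits are run by the questionnaire investigator. The article never says that this investigator takes consent, and the Blinding section separates that role from intervention and analysis. If the two are the same person, assessor blinding is also at risk; otherwise it is not affected by this route.

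On timing, Trial status gives a start on May 27, 2020 and an anticipated end of recruitment on September 25, 2020. The article appeared in July 2021 and puts list access in the past tense, while still describing recruitment as ongoing. Changing who holds the list may therefore come too late for some or all patients.

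**Conclusion.** The concern holds in this form: as written, concealment does not cover those who take consent, and no safeguard against foreknowledge is described, so selection bias is possible. This rests on reading the signing researchers as those who obtain consent, which is the natural reading beside the recruitment section.

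Actual non-concealment, use of the list in eligibility decisions and unblinding of the assessor are not established. The size of any bias cannot be estimated from the article. The 11% to 23% range is conditional on an assumed imbalance of 3 to 5 points and a back-calculated SD, and should not be read as this trial's error rate. The point still matters because it touches the primary comparison and could not be fully repaired in the analysis.

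**What to change.** **For any patients still to be randomized**

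- Give the sequence to a team member or system outside consent and assessment.
- Release one assignment at a time, only after eligibility, consent and baseline questionnaires are recorded. Under Baseline visit, the questionnaires are described after randomization.
- Bar consent-takers and questionnaire assessors from the list.

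**For patients already randomized**

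- State who could see the sequence, and when. Say whether those people also applied the exclusion criteria or administered questionnaires.
- Correct the sentence if assignments were in fact released one at a time.
- Report the baseline comparison by arm, giving weight to items fixed before allocation, such as APACHE II, SOFA and ICU length of stay. Balance on these would be reassuring but would not rule out selection on unmeasured factors.
- Name possible selection bias as a limitation.

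**Cost.** No extra patients or visits are needed. The change of list holder is procedural; the article describes its electronic database only for data entry, so whether it can also release assignments would have to be checked. If enrolment has closed, what remains is disclosure, a corrected sentence and a baseline table drawn from data already being collected.

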#### Control group

Standard-of-care is as follows: patient follow-up will be carried out by their referring physicians (primary care physicians or specialists), who will not be involved in the study. After the baseline visit, the second and third visits will be phone call visits at 3 and 6 months after hospital discharge.

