### Data analysis

Qualitative variables will be presented as proportions, while for quantitative variables, the mean (standard deviation) or median (interquartile range), after checking for normality using the Shapiro-Wilk test, will be used. To compare variables across groups, Student *t* tests or Mann-Whitney *U* tests for continuous data and chi-square tests or exact tests for categorical variables will be carried out. Before parametric hypothesis testing, equality of variances will be studied using the Levene’s test, and if assumptions are not met, contrasts will be performed with the Welch’s test. An intention-to-treat approach will be followed. Two-tailed *P* values will be presented and a significance level of 0.05 will be used.

For the secondary outcomes, adjustment with the Benjamini-Hochberg procedure will be carried out.

A sub-analysis of the effect of treatment on compliers will be performed for the main outcome. Compliers are defined as those subjects that effectively receive the treatment they are allocated to. For the present study, compliers will be defined as individuals that, having been randomized to the intervention, complete at least two out of three medical visits and at least five out of seven psychological interventions. For the statistical analysis, instrumental variable analysis will be carried out. A two-sided probability (*p*) value of less than 0.05 will be considered to indicate statistical significance. The statistical analysis was performed using R (https://www.rstudio.com/) statistical software.

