## Discussion

As far as we know, this is the first randomized clinical trial that examines the effectiveness of an early care therapeutic education and psychological intervention for the management of post-intensive care syndrome and chronic pain after COVID-19.

Patients who survive a critical illness often experience disturbances in many areas, with pain being one of the most important topics. Unfortunately, lack of adequate care to manage this pain is often a problem during the patients stay in the units [5]. This study would quantify the impairment on quality life after ICU admission, as well as the incidence of chronic pain, anxiety, depression, and PTSD. The health status derived from our analysis could be used in economic evaluations of healthcare systems and long-term impact and consequences of the pandemic. Likewise, if the effectiveness of our intervention is verified, it would serve as proof of the need to implement early care programs that allow the recovery process to be followed from early stages, given the current scenario of the pandemic.

Being an integral part of this syndrome, and in order to avoid the limitations and effects of pain on the patient’s quality of life, pain management should be introduced in the ICU.

This project has some limitations.

The main one is that patients meeting inclusion criteria (especially those who have had a more severe course of the disease) may have a severe mobility limitations that would prevent them from attending some trial visits, which would result in a selection bias. This would add to the problem of a small population sample as a consequence of the study being carried out in a single center.

In addition, there are risk factors associated with the development of PICS and chronic pain after a critical illness. These include older age, low socioeconomic status, female gender, previous mental health problems, negative ICU experiences, and delirium.

Therefore, an exploratory analysis of risk factors potentially associated with PICS due to COVID-19 will be carried out, although the sample size will be a determining factor in the conclusions

Future development of multi-center projects may overcome this limitation.

Finally, since this intervention program involves face-to-face visits, the pandemic could limit its correct development.

Restrictions on mobility might make hospital follow-up visits difficult.

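### The protocol does not say that the 6-month outcome is still sought from intervention patients who stop the programme or cannot attend, while controls are phoned, so the primary comparison is exposed to differential loss

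*Protocol article*

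**What the plan says.** All references are to the protocol article.

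- *Methods of randomization and bias minimization* holds the retention text. Before people leave: "Patients will be encouraged to remain in the study during each interview by giving them feedback about the importance of their collaboration". Once they leave: "Participants who decide to drop out during follow-up will be asked about the reason for it, and all their answers will be recorded". The section draws no line between stopping the programme and leaving follow-up.
- *Control group* fixes how controls are reached: "After the baseline visit, the second and third visits will be phone call visits at 3 and 6 months after hospital discharge". No matching sentence gives the contact mode for the intervention arm.
- *Baseline visit* sets the programme at three medical visits (4 to 6, 8 and 18 weeks after discharge), plus seven weekly sessions of 90 minutes for patients who meet the depression-score criterion.
- *Discussion* says of the more severe cases that they "may have a severe mobility limitations that would prevent them from attending some trial visits, which would result in a selection bias". It adds that "since this intervention program involves face-to-face visits, the pandemic could limit its correct development" and that "Restrictions on mobility might make hospital follow-up visits difficult".
- *Data analysis* says "An intention-to-treat approach will be followed" and names two-sample tests (Student, Welch or Mann-Whitney) for continuous outcomes. It adds an instrumental-variable analysis of compliers.
- *Sample size* allows for 20% loss, not split by arm.

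**The concern.** The effort needed to stay in contact differs by arm. After baseline, a control has to answer two phone calls. An intervention patient is asked to attend further medical visits and possibly seven sessions, and is not promised a phone call if attendance fails. The article itself expects that the more disabled patients may be unable to attend. It offers no remedy, although phone contact is already the routine for the other arm. Encouragement given during interviews cannot reach someone who has stopped coming.

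If non-attendance also costs the 6-month questionnaire, the intervention mean is computed on patients well enough to attend, while the control mean rests on a less selected group. A two-sample test uses only patients with a 6-month value, so randomisation would no longer protect the comparison. No later analysis can recover outcomes that were never collected, so this belongs in the protocol.

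**Working it through.** **The plan's own figure.** The allowance for loss reproduces: 42 × 1.2 = 50.4, rounded up to 51 per arm, 102 in total. With 20% loss, 51 × 0.8 = 40.8 per arm remain. The allowance protects power. It does nothing about who is lost.

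**Implied SD.** The article states no SD. Assume that the 20% difference means 20% of the control mean of 50, so 10 points. With one-tailed 0.05, 80% power and 42 per arm, as in *Sample size*:

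SD = √[42 × 10² / (2 × (1.645 + 0.842)²)] = 18.4.

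Reading the same size as two-sided (1.96 in place of 1.645) gives 16.4.

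**Bias among patients with data.** Suppose lost patients score *g* points below retained patients in either arm. The retained mean then exceeds the full-arm mean by loss × *g*, and

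bias = (loss in intervention − loss in control) × *g*.

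**Chance of rejecting a true null** at two-sided 5%: P(|Z + bias/SE| > 1.96), with SE = 18.4 × √(1/n_I + 1/n_C) and n = 51 × (1 − loss). Loss by arm and *g* are not in the article; every value below is an assumption.

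| Loss, intervention / control | *g* | Bias | SE | Rejection |
|---|---|---|---|---|
| 20% / 20% | 15 | 0 | 4.07 | 5.0% |
| 20% / 10% | 10 | +1.0 | 3.96 | 5.7% |
| 20% / 5% | 15 | +2.25 | 3.91 | 8.9% |
| 25% / 5% | 20 | +4.0 | 3.98 | 17.1% |
| 5% / 20% | 15 | −2.25 | 3.91 | 8.9%, mostly against the programme |

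With SD 16.4, the three positive rows give 5.9%, 9.9% and 20.4%.

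Those three rows average 15%, 12.5% and 15% loss, below the planned 20%. Bias depends on the difference in loss and not on its level: 27.5% against 12.5%, which averages 20%, with *g* = 15 again gives 0.15 × 15 = 2.25.

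**A second model.** Let staying in the study correlate ρ with the 6-month EQ-VAS. An arm with loss p is then shifted by ρ × SD × φ(z_p)/(1 − p). The last factor is 0.350 at p = 0.20 and 0.195 at p = 0.10.

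- 20% loss related to outcome in the intervention arm, control loss unrelated: ρ = 0.3 gives 1.7 to 1.9 points and ρ = 0.5 gives 2.9 to 3.2 (SD 16.4 to 18.4).
- 20% against 10%, same ρ of 0.3 to 0.5 in both arms: 0.8 to 1.4 points.
- Same loss and same ρ in both arms: 0.
- Extreme case, the worst 20% of the intervention arm all lost and control loss unrelated: 5.7 to 6.4 points.

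**The case against.** A reader might infer that the sickest intervention patients drop out of the primary endpoint and that the result is biased towards the programme. The article does not support that as fact.

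- The sentence on dropout covers people who choose to leave, in either arm. It does not say that patients who stop the programme, or cannot attend, lose their outcome assessment.
- *Outcome measurements* schedules the EQ-5D-5L at 3 and 6 months without tying it to attendance.
- *Blinding* gives the questionnaires to an investigator outside the programme, and no programme visit falls at 6 months. A missed session need not mean a missing questionnaire.
- The complier analysis needs outcomes from intervention patients who did not comply, so the authors appear to expect them.
- The contact mode for the intervention arm is not stated, and the schedule figure is not available here. The remark on selection bias names no arm and may partly concern enrolment. Patients hard to follow are excluded before randomisation.
- Size and direction rest on assumed loss. Controls with little contact could be lost more often.

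All of this stands against the stronger reading. It also shows that the means to collect the outcome exist: a separate assessor, separate timing, and a phone routine. What remains is that no sentence commits to using them for intervention patients who stop or cannot come, in a trial that names non-attendance as its main weakness.

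Detailed missing-data methods may sit in an analysis plan not shown, and their absence is not held against the article. The model suggested below is an improvement on the tests that the article names.

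**Conclusion.** The concern holds as an exposure and not as a demonstrated bias. The recorded-reason rule, phone contact stated for controls only, and the acknowledged attendance problem together leave the 6-month comparison open to loss that differs by arm and by severity. Bias in favour of the programme is the most plausible direction, because after baseline the attendance burden falls on that arm, but it is not certain.

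The size cannot be derived from the article. It is zero if the rate and mechanism of loss are alike in both arms, and negative if controls with poor outcomes are lost more. It is about 1 to 4 points under the assumed differential losses, which is 10% to 40% of the 10-point target. Those cases raise the two-sided false-positive rate from 5% to between about 6% and 17% at the implied SD of 18.4. The protocol should be changed because the remedy is cheap and the outcome cannot be recovered afterwards.

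**What to change.** Extend the dropout sentence in *Methods of randomization and bias minimization* along these lines: *A patient who stops the medical visits or psychological sessions, or cannot attend in person, remains in the trial. Outcomes at 3 and 6 months are sought from every randomised patient who has not withdrawn consent to contact, whatever their programme attendance, by the same phone contact in both arms. The date of and reason for stopping the programme are recorded separately from withdrawal from follow-up.* If in-person assessment is kept for the intervention arm, say so, and use the phone at least for those who cannot attend.

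In *Data analysis*, make the primary comparison a model of EQ-VAS that uses the baseline and 3-month values already collected, so that patients lost after 3 months still contribute. This assumes that the remaining loss is explained by those earlier values. Report loss by arm.

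The cost is a short amendment and a few extra calls by the investigator who already gives the questionnaires. If only non-attenders are phoned, contact mode will vary with severity within the intervention arm. Phoning everyone in both arms avoids that.
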